## Methods

2

### Overall trial design

2.1

This project employs an open-label, parallel-group randomized controlled trial (RCT) stratified by suicidal ideation to evaluate the effectiveness of the Bud app intervention. The trial will be conducted in accordance with the CONSORT (CONsolidated Standards Of Reporting Trials) 2025 Statement. Participants (N = 302) will be randomly allocated to either the Intervention group (Bud app; n = 151) or the active Control group (mental health factsheets; n = 151). Intervention group participants will have access to the Bud app content and features for four weeks. They will be encouraged to use it at least once per week, but may engage with it as much or as little as they choose. Control group participants will receive access to four mental health fact sheets over the same timeframe. All content in both conditions will be delivered in English. Assessments will occur at baseline (T1), two weeks post-baseline (T2), and post-intervention (four weeks post-baseline; T3), enabling the analysis of intervention effects both within and between groups over time.

### Sample size

2.2

The target sample size of 302 participants (151 per group) was determined through an a priori power analysis conducted using the SIMR package in R [41]. We simulated 1000 datasets for a 2 (intervention vs. control) × 3 (T1, T2, T3) repeated-measures linear mixed-effects model—with fixed effects for group, time, and their interaction, random intercepts, moderate correlations, and a nonsphericity correction factor of 1. Specifying a moderate Group × Time interaction (f ≈ 0.25) at α = 0.05, we found that 252 participants (126 per group) would yield ∼80 % power; inflating for an anticipated 20 % attrition rate resulted in a final sample target of N = 302 (151 per group).

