#### Main analyses

2.10.2

Changes in the primary and secondary outcomes will be evaluated using generalised linear mixed models (GLMMs), including random intercepts for participants, random slopes for time, and fixed effects for group, time, and their interaction. For zero-inflated outcomes such as suicidal ideation (e.g., a large number of individuals reporting no ideation), model diagnostics will be used to assess the appropriateness of the GLMM approach, with consideration of alternative specifications (e.g., two-part models such as the zero-inflated Poisson model) if indicated [60,61]. Measures of acceptability and iatrogenic effects will be assessed with descriptive statistics. Pearson correlations will explore associations between app engagement and mental health outcomes. Exploratory analyses will investigate potential moderators, including demographics (e.g., gender and country of origin) and emotion regulation, for the primary and secondary outcomes, as well as for the engagement and acceptability measures. Sensitivity analyses will be conducted to assess whether outcome patterns differ as a function of intervention engagement or baseline stratification levels of suicidal ideation.

Interview data will be analyzed using a rapid qualitative coding analysis, drawing on principles of Framework Analysis [62,63]. This method is well-suited to small samples and time-sensitive evaluations, allowing for systematic and transparent interpretation of participant feedback across key domains [63]. A deductive coding framework will be developed based on the study aims (e.g., app acceptability, usability, engagement, and perceived impact), while remaining open to inductive insights raised by participants. Data will be summarised within NVivo to facilitate cross-case comparisons and identification of common themes and divergent experiences. This approach balances rigour and practicality and is commonly used in applied health and digital mental health research. Analysis will begin once all interviews are completed.

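### Read as Cohen's f, the stated effect of 0.25 does not fit 252 participants at about 80 % power, and the power model omits the random slopes of the planned analysis

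*Protocol article*

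**What the plan says.** Section 2.2 (Sample size) of the protocol article reports 1000 SIMR datasets for a "2 (intervention vs. control) × 3 (T1, T2, T3) repeated-measures linear mixed-effects model". The simulated model is described as having "random intercepts, moderate correlations, and a nonsphericity correction factor of 1". On the effect and the sample size it says "Specifying a moderate Group × Time interaction (f ≈ 0.25) at α = 0.05, we found that 252 participants (126 per group"), and that this "would yield ∼80 % power". An allowance for 20 % attrition then brings the target to 302.

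Section 2.2 does not give the value of the correlation, the coding of time, the contrast tested or the SD by which the effect was standardised.

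Section 2.10.2 (Main analyses) plans mixed models with "random intercepts for participants, random slopes for time", plus fixed effects for group, time and their interaction. H1 in Table 1 concerns the difference in distress reduction at post-intervention, which is T3.

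**The concern.** An f of 0.25 is the conventional medium value of Cohen's f, and the article calls the effect moderate. A medium interaction in a design with three repeated measures normally needs far fewer than 252 participants for 80 % power, so effect, sample size and power do not seem to belong together.

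The detectable effect is what a reader needs to interpret a null result. On the printed text, a null result would speak only against a moderate effect, with 80 % power. If the effect simulated was much smaller than f = 0.25, the trial is aimed at a different target from the one stated. If it really was f = 0.25, the power is understated. The second difference, random intercepts in the power model against intercepts and slopes in the analysis, bears on whether the 80 % holds for the model that will be fitted.

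**Working it through.** **Inputs.** From section 2.2: two groups, three time points, f = 0.25, α = 0.05, nonsphericity factor 1, N = 252 (126 per group), power about 80 %, attrition 20 %. Assumed, because the article gives no number: correlation r between assessments of 0.3 to 0.7, central value 0.5, with 0 also tried.

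**1. Reproducing the stated figure with Cohen's f.** Noncentral F for the interaction has df1 = 2 and df2 = 2(N − 2) = 500 at N = 252. The conventions differ in the noncentrality λ:

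| Convention | λ at N = 252 | Power at 252 | N for 80 % |
|---|---|---|---|
| Default repeated measures, λ = 3f²N/(1 − r), r = 0 | 0.0625 × 252 × 3 = 47.25 | > 99.9 % | 54 |
| Same, r = 0.3 / 0.5 / 0.7 | 67.5 / 94.5 / 157.5 | > 99.9 % | 38 / 28 / 18 |
| λ = f² × df2 | 0.0625 × 500 = 31.25 | 99.9 % | 82 |
| λ = f²N | 0.0625 × 252 = 15.75 | 95.3 % | 156 |
| Two groups, one measurement, d = 2f = 0.5 (df1 = 1) | 15.75 | 97.7 % | 128 |

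None gives 252 at 80 %. The Monte Carlo standard error with 1000 datasets is √(0.8 × 0.2/1000) = 1.3 percentage points, too small to turn 95 % into 80 %. Conversely, 80 % power at 252 corresponds to f of about 0.06 to 0.11 (default convention, r = 0.7 to 0), 0.14 (λ = f² × df2) or 0.20 (λ = f²N).

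**2. A reading that does reproduce it.** SIMR takes effects as model coefficients. Suppose the interaction coefficient is 0.25 per assessment step, the residual SD is 1, intercepts are random and time is linear. With three equally spaced visits the slope is (T3 − T1)/2, with residual variance 2/4 = 0.5 per person.

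- SE of the slope difference = √(2 × 0.5/126) = 0.0891
- z = 0.25/0.0891 = 2.806
- Power = Φ(2.806 − 1.960) = Φ(0.846) = 80.1 %

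A check with 4000 simulated datasets gave 79 to 80 %. A T3 coefficient of 0.5 residual SD with a one-degree-of-freedom test gives the same result. A two-degree-of-freedom test of this pattern has only about 71 %.

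In terms of Cohen's f, the group differences are 0, 0.25 and 0.5. Centred over time and halved they are −0.125, 0 and 0.125, with root mean square 0.125 × √(2/3) = 0.102 residual SD. Multiplying by √(1 − r) to reach total SD gives f = 0.102, 0.085, 0.072 and 0.056 at r = 0, 0.3, 0.5 and 0.7. The T3 difference is 0.5 × √(1 − r), which is 0.35 total SD at r = 0.5.

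**3. Random slopes.** Keep step 2 and add a slope variance s (assumed; the residual variance stays at 1). SE = √(2(0.5 + s)/126):

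- s = 0.05: power 76 %
- s = 0.10: power 73 %
- s = 0.20: power 66 %

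These figures add variance to the T1-to-T3 change. If the simulated correlation already reflected that change, nothing is lost on the linear contrast.

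**4. What 302 leaves.** 302 × 0.8 = 241.6, about 242 completers or 121 per group. (302 is 252 × 1.2; dividing 252 by 0.8 would give 315.) The T3 difference detectable with 80 % power is (1.960 + 0.842) × σ × √(2/121) = 0.360 × σ in baseline SD units:

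- Change scores, σ = √(2(1 − r)): 0.43, 0.36 and 0.28 SD at r = 0.3, 0.5 and 0.7
- Baseline-adjusted, σ = √(1 − r²): 0.31 SD at r = 0.5

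**The case against.** The strongest reply is that the simulation may be sound and only its label wrong. Step 2 lands on exactly 126 per group, so a valid sample size with a misnamed effect is a credible explanation. This stands, and it limits the point. A reader might infer from step 1 that 252 is the wrong number, or that the trial is overpowered or underpowered. The article supports none of these: the answer depends on the metric behind 0.25, which is not stated. It does not rescue the text, because a coefficient of 0.25 residual SD per step is not f = 0.25.

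A reader might also infer that random slopes certainly reduce power, to between 66 % and 76 %. That goes too far. With three balanced, equally spaced visits, the standard error of the linear contrast depends only on the variance of the T1-to-T3 change. Slopes cost power only if they add to the change variance that was simulated. The article gives no slope variance. Nor does the model difference explain step 1: with a true f of 0.25 (linear pattern, r = 0.5, residual variance 0.5), power stays above 80 % up to a slope variance of about 2.5.

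Finally, a condensed article may leave variance components to a fuller document. Their absence alone is no error. The point rests on printed figures that conflict and on two printed models that differ.

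**Conclusion.** The point holds in limited form. As written, f ≈ 0.25 taken as Cohen's f, N = 252 and about 80 % power cannot all be true: power at 252 would be about 95 % to over 99.9 %. This needs no assumption about the correlation beyond a value from 0 to 0.7. Mislabelling of a raw coefficient is a possible source, but it rests on an assumed residual SD of 1 and a one-degree-of-freedom test, and the article does not confirm it.

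The difference between the power model and the analysis model is plain from sections 2.2 and 2.10.2. Its cost is conditional, and its size is an assumption. What is established is that the effect, its label and the model behind 252 must be reconciled. It is not established that the sample size is inadequate.

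**What to change.** In section 2.2, replace the f value and the word moderate with the effect actually simulated: a T3 difference in K10 SD units, with the tested contrast and the assumed correlation. Rerun the simulation with the section 2.10.2 model, random slopes included, the T3 contrast of H1 and 20 % attrition, over a stated range of slope variances.

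Without enrolling more, restate the effect detectable with 80 % power for the roughly 242 completers that 302 leaves. At an assumed correlation of 0.5 and before any extra slope variance, this is about 0.36 SD for change scores or 0.31 SD with baseline adjustment. Over correlations of 0.7 to 0.3 it is 0.28 to 0.43 SD for change scores.

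The cost is about half a day of simulation and a few sentences of text.

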## Abstract

International students face elevated risk for mental health problems and suicide, yet encounter multiple barriers to accessing timely and culturally responsive treatments. Key challenges include high rates of psychological distress, low mental health literacy, and reduced help-seeking, often compounded by perceived burdensomeness, a lack of belonging, and difficulties with emotion regulation. Bud is a self-guided, co-designed mobile app developed to address these challenges through an accessible digital intervention. This paper outlines a protocol for a randomized controlled trial evaluating the effectiveness, acceptability, engagement, and safety of Bud among international students enrolled at Australian tertiary institutions. The trial also includes an internal pilot phase to ensure the feasibility of the trial procedures, with benchmarks for recruitment, retention, and engagement. A community sample of 302 participants will be randomly assigned to either the intervention group (Bud app) or the active control group (online mental health fact sheets) for four weeks. Assessments will be completed online at baseline, two weeks, and four weeks post-baseline. The primary outcome is psychological distress, with secondary outcomes including help-seeking intentions, perceived burdensomeness and belonging, emotion regulation, mental health literacy, and suicidal ideation. Acceptability and engagement will be assessed using self-report and objective measures. Interviews will be conducted with a subset of 20 participants to explore their views on Bud further. This trial will provide the first evaluation of a suicide prevention tool specifically for international students. If effective, Bud could offer a scalable and culturally relevant solution to improve student mental health and reduce service access barriers.

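### The 20 % attrition allowance multiplies 252 by 1.2 instead of dividing by 0.8, so 302 enrolled leaves about 242 with complete follow-up; the effect on power is small

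*Protocol article*

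**What the plan says.** Section 2.2 (Sample size) of the protocol article gives the derivation in two steps.

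- Simulation step, for a group-by-time interaction in a linear mixed model with random intercepts: "we found that 252 participants (126 per group) would yield ∼80 % power".
- Attrition step: "inflating for an anticipated 20 % attrition rate resulted in a final sample target of N = 302 (151 per group").

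The enrolment target is used elsewhere without reference to attrition. Section 2.1 (Overall trial design) says "Participants (N = 302) will be randomly allocated", and the Abstract speaks of "A community sample of 302 participants".

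Section 2.10.3 (Missing data) says that missing outcomes are handled by maximum likelihood within the mixed models, so that all available data are used without imputation.

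**The concern.** The three numbers in section 2.2 (252, 20 % and 302) do not agree with each other. An allowance for attrition is meant to leave the required number after the expected loss. Taking 20 % off 302 does not return 252. The article states no other inflation rule and no lower attrition rate that would explain 302, and a gap of 13 to 14 participants is too large for rounding.

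At stake is whether the stated derivation supports the claim that the trial keeps about 80 % power if the anticipated attrition occurs. The attrition allowance is the only provision for loss to follow-up in the sample size derivation. The primary hypothesis (H1, Table 1) is about the post-intervention comparison, the time point most exposed to dropout.

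**Working it through.** **Inputs, all from section 2.2:** required number 252 (126 per group); power about 80 % at 252; α = 0.05; anticipated attrition 20 %; target 302 (151 per group); 1000 simulated datasets.

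**Step 1. Reproduce the plan's figure.**
- 252 × (1 + 0.20) = 302.4, stated as 302.
- 126 × (1 + 0.20) = 151.2, stated as 151.

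Both match, so the rule that was used can be identified.

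**Step 2. Apply the usual rule, n / (1 − attrition).**
- 252 / 0.80 = 315.
- 126 / 0.80 = 157.5, rounded up to 158 per group, or 316 in total.
- Difference from 302: 13 (from 315) to 14 (from 316).

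**Step 3. Check what 302 delivers.**
- 302 × 0.80 = 241.6 (120.8 per group), which is 252 − 241.6 = 10.4 short.
- Largest attrition that still leaves 252: 1 − 252/302 = 16.6 %.

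**Step 4. Power if only complete cases count.** Take 80 % at 252 as given and scale the noncentrality by 241.6/252. For a two-sided 1-df test (the article does not state sidedness):
- Φ[(1.960 + 0.842) × √(241.6/252) − 1.960] = 78.3 %.
- The 2-df chi-square version gives 78.2 %.

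**Step 5. Power in a mixed model that keeps partial data.** Assumptions: 302 randomised, 20 % without T3, random-intercept (compound-symmetry) covariance as in section 2.2, and data missing at random. Power is for the group difference in change from T1 to T3 (1 df), anchored to 80 % at 252 complete. Section 2.2 calls the correlations only moderate, so the range 0.3 to 0.7 is an assumption.

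| Dropouts contribute | r = 0.3 | r = 0.5 | r = 0.7 |
|---|---|---|---|
| T1 only | 81.2 % | 80.4 % | 79.5 % |
| T1, and T2 for half of them | 81.3 % | 80.7 % | 80.2 % |
| T1 and T2 | 81.5 % | 81.0 % | 80.7 % |

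For the T1-only row, the 2-df test gives 81.3, 80.4 and 79.5 %.

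**Step 6. Simulation error in the plan's own figure.** With 1000 datasets, the standard error at 80 % is √(0.8 × 0.2 / 1000) = 1.26 points, so the 95 % interval is about 77.5 to 82.5 %.

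**Not computed.** Section 2.10.2 (Main analyses) adds random slopes for time. Their variance is not given, so Step 5 cannot be repeated for that model.

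**The case against.** The strongest reply is that the trial does not plan a completers-only analysis. Section 2.2 powers a mixed model, and section 2.10.3 keeps dropouts' earlier measurements. On that basis 302 with 20 % lost still gives about 80 % power (Step 5). Even the completers-only figure of about 78 % lies within the simulation error of a power that the plan itself calls approximate (Step 6). The plan also speaks of 252 participants and never calls them completers.

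Most of this stands, and it settles the size of the problem. It does not repair the derivation. Section 2.2 does not rest 302 on partial data and describes no dropout in the simulation; it presents 302 as the result of inflating 252 for 20 % attrition, and it is not. Counting the 252 as people who remain after attrition is the natural reading of such an inflation, though the text does not spell it out.

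A reader might infer two stronger things.

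- **That the trial fails to deliver 80 % power after 20 % attrition.** The documents do not support this, because it holds only for an analysis that discards partial data.
- **That 302 is a wrong figure wherever it appears.** It is a consistent enrolment target in the Abstract and in section 2.1, where no attrition claim is attached to it. Only the attrition clause in section 2.2 is at fault.

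**Conclusion.** The error is certain and minor. The attrition step uses the wrong operation, and 302 falls 13 to 14 short of what 20 % attrition requires if 252 are to remain. About 242 would have complete follow-up.

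The cost is just under 2 power points on a completers-only count. In the random-intercept model with partial data kept, power is within about half a point below to 1.5 points above 80 %. That second result rests on the assumed correlations of 0.3 to 0.7, on data missing at random, and on accepting the plan's 80 % at 252. That starting figure comes from a simulation whose variances and correlations are not reported, and it was not re-derived here. The result does not extend to the random-slope model.

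The error introduces no bias and gives no reason to change recruitment or the analysis.

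**What to change.** Keep N = 302 and correct the attrition clause in section 2.2 in one of two ways.

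1. State that 302 enrolled retains 252 participants at up to 16.6 % attrition.
2. State that 20 % attrition leaves about 242 with complete follow-up, and that about 80 % power then relies on the mixed model's use of partial data. Support this by rerunning the simulation with 20 % dropout built in, preferably under the random-slope model of section 2.10.2.

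A bare statement that power is 78 % should be avoided, because it would misdescribe the planned analysis.

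If the sponsor wants 252 with complete follow-up at 20 % attrition, the target becomes 316 (158 per group), which is 14 more participants; the Abstract and section 2.1 would then change too.

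Option 1 costs one clause and a less favourable attrition tolerance. Option 2 costs one clause and one simulation run. With 302 kept, the Abstract and section 2.1 stay as they are. The registry record was not available, so whether it repeats the attrition statement is unknown.

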### Study sites

2.3

The study will be led by researchers at Orygen, the Centre for Youth Mental Health (CYMH) at the University of Melbourne. However, there are no specific study sites, as participants will be from a community sample and will access the interventions remotely using their mobile phones. Both interventions are designed to be used flexibly, allowing participants to engage at times and locations that are convenient for them. All study data will be collected through online surveys administered via REDCap.

### Participants

2.4

#### Inclusion criteria

2.4.1

To be eligible for the study, participants must be international students currently enrolled at an Australian tertiary education institution and residing onshore in Australia. They must be 18 years or older, able to read and speak English and have access to a smartphone running either Android or iOS. Suicidal ideation was not required for inclusion, as Bud is designed as a community-level, upstream suicide prevention program for international students.

#### Exclusion criteria

2.4.2

There are no predefined exclusion criteria for the study. However, a safety management protocol is in place. Participants who indicate suicide risk during surveys, request a phone check-in, and are assessed as being at imminent risk of harm during the screening call will be withdrawn from the study and referred to appropriate support services. Participants with ongoing suicidal ideation who do not report imminent risk may remain in the study.

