	***Secondary outcomes***
	*H2:* Participants using Bud will report greater increases in help-seeking intentions compared to the control group at post-intervention.
	*H3:* Participants using *Bud* will report greater reductions in perceived burdensomeness and thwarted belongingness compared to the control group at post-intervention.
	*H4:* Participants using *Bud* will report greater improvements in emotion regulation compared to the control group at post-intervention.
	*H**5**:* Participants using *Bud* will report greater increases in mental health literacy from the intervention than the control group.
	*H6:* Participants using *Bud* will report greater reductions in suicidal ideation compared to the control group.
**Aim 2:** To assess the acceptability of the Bud app among international student users	*H7:* Participants in the Bud group will rate the app as acceptable, including positive evaluations of its engagement, functionality, aesthetics, information quality, and overall subjective quality.
**Aim 3:** To assess engagement with the Bud app	*H8:* Participants in the Bud group will demonstrate high engagement, reflected in app usage metrics and perceived helpfulness of activities.
**Aim 4:** To assess the safety of the Bud app	*H9:* No iatrogenic effects (e.g., increases in suicidal ideation or psychological distress) will be observed or reported among participants in the Bud group.

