
**Table 2 tbl2:** Study measures at each time point.

Domain	Measure	# items	T1	T2	T3
Descriptive information	Demographic questionnaire	14	X		
	Previous Suicide attempts	2	X		
	Previous self-harm behaviours	1	X		
	Adjustment to University: CAQ [48]	14	X		
	Adverse Childhood Experiences: ACEs [49]	11	X		
Primary outcome	Psychological Distress: K10 (50)	10	X	X	X
Secondary outcomes	Help-Seeking: GHSQ [51]	12	X	X	X
	Perceived Burdensomeness: INQ [52]	5	X	X	X
	Sense of Belonging: INQ [52]	5	X	X	X
	Emotion Regulation: DERS – SF [53]	18	X	X	X
	Suicidal ideation: YSIS-3 (45)	3	X	X	X
	Mental health literacy: MHLS-9 (54)	9			X
Acceptability & iatrogenic effects	Open feedback question	1	X	X	X
	Acceptability and Iatrogenic effects: Custom Measure	6			X

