	***Intervention group only***				
	App usage (number and time accessing)	App metric		X	X
	Number and type of activities completed	App metric		X	X
	Perceive helpfulness of activities	In-app self-report		X	X
Total # of survey items per group			I = 96	I = 54	I = 92
			C = 96	C = 54	C = 69

Note: I = Intervention group, C = Control group. Each measure is described in detail below.

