### Safety management

2.11

A structured safety protocol is in place to monitor and respond to participant distress and suicide risk. Mental health support information, including crisis contacts and interpreter options, is provided multiple times, including in the app, on the control factsheets, survey completion screens, and PICF. At T1, T2, and T3, participants complete the Kessler Psychological Distress Scale (K10) and are asked if they are having thoughts of suicide (YSIS-3). At T2 and T3, they are additionally asked whether the app, factsheets, or surveys made them feel suicidal or want to self-harm. If a participant scores ≥30 on the K10, endorses suicidal ideation, or reports distress caused by study content, they are offered a wellbeing check-in and provided a list of relevant support resources they can contact. If they accept the check-in, a trained team member experienced in suicide risk assessments will review relevant data (e.g. suicidal ideation score from YSIS-3) and conduct a phone-based risk assessment within two business days. Suicide risk will be based on the phone assessment across four levels (none, low, moderate, high/life-threatening), and appropriate responses will be initiated, including emergency services if necessary (See Table 4). A study psychologist will be available to support staff conducting the risk assessments as required. Participants at life-threatening risk will be withdrawn from the study. Participants at other risk levels are reminded of support options and asked whether they wish to continue in the study.

**Table 4 tbl4:** Suicide risk levels and associated responses.

Risk Level	Definition	Action
None	No current suicidal thoughts or behaviour; participant reports no distress linked to study participation.	No action required beyond standard follow-up and support information.
Low	Passive thoughts of death or fleeting suicidal ideation without intent, plan, or significant distress.	Participant encouraged to access supports (e.g., helplines, psychologist) as required. Check whether they wish to continue in study.
Moderate	Suicidal ideation present with some associated distress, but no immediate plan or intent to act; participant can ensure their safety.	Participant encouraged to access supports (e.g., helplines, psychologist) as required. Check whether they wish to continue in study.

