High/Life-Threatening	Active suicidal ideation with a plan, intent, or expressed inability to stay safe.	Initiate emergency response, withdraw participant, consult study psychologist.

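### The T2 harm question in section 2.11 is missing from Table 2, and study withdrawal at imminent risk leaves people selected on high suicide risk out of the T3 harm summary for H9

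*Protocol article*

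**What the plan says.** **Harm question.** Section 2.11 states: "At T2 and T3, they are additionally asked whether the app, factsheets, or surveys made them feel suicidal or want to self-harm". It then lists three triggers for a check-in. Besides a K10 score of 30 or more, the rule applies if a participant "endorses suicidal ideation, or reports distress caused by study content, they are offered a wellbeing check-in". Table 2 (section 2.9) has one row for harm items, "Acceptability and Iatrogenic effects: Custom Measure", with 6 items marked at T3 only. The row "Total # of survey items per group" prints 96 at T1, 54 at T2, and at T3 92 (intervention) and 69 (control).

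**Withdrawal.** Section 2.4.2 covers participants who indicate risk in a survey and ask for a call: those "assessed as being at imminent risk of harm during the screening call will be withdrawn from the study". Section 2.11 repeats the rule: "Participants at life-threatening risk will be withdrawn from the study". For the highest risk level, Table 4 says: "Initiate emergency response, withdraw participant, consult study psychologist". Section 2.8 encourages follow-up surveys whatever the use of study materials, but does not mention withdrawn participants.

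**Use of the data.** H9 in Table 1 reads: "No iatrogenic effects (e.g., increases in suicidal ideation or psychological distress) will be observed or reported among participants in the Bud group". Section 2.10.2 summarises the acceptability and iatrogenic measures descriptively. Section 2.9 adds changes in suicidal ideation and adverse-event monitoring as further evidence.

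**The concern.** T2 is the only scheduled survey during the four weeks of exposure. If the surveys follow Table 2, a participant with K10 below 30 and no ideation who was upset by the content has no specific question at T2 that would prompt a check-in offer. Only the free-text item could reveal it. If they follow section 2.11, that gap closes, but the table is wrong.

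The withdrawal rule raises a separate issue that correcting the table does not remove. It ends participation, not merely use of the app or fact sheets, because of an event after enrolment that is closely tied to what H9 is about. The custom harm items exist only at T3. Anyone withdrawn earlier is absent from that summary, and the absence depends on suicide risk. For a hypothesis worded as no effects observed or reported, one or two people can change the message.

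**Working it through.** **Step 1: reproduce Table 2.** Item counts are those printed in the table.

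- Repeated outcomes: K10 10 + GHSQ 12 + INQ burdensomeness 5 + INQ belonging 5 + DERS-SF 18 + YSIS-3 3 = 53.
- T1: 14 + 2 + 1 + 14 + 11 + 53 + 1 open item = 96 (printed 96).
- T2: 53 + 1 open item = 54 (printed 54).
- T3 control: 53 + 9 + 1 + 6 = 69 (printed 69).
- T3 intervention: 69 + 2 + 20 + 1 = 92 (printed 92).

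All four totals reproduce exactly, so the table was read correctly and the T2 total has no room for another item. One harm question would make it 55, and the whole custom measure 54 + 6 = 60. The open item is also asked at T1, before any exposure, so it is not the question that section 2.11 describes.

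**Step 2: what a withdrawn participant does not give.** At T3: 6 custom items + 10 K10 + 3 YSIS-3 = 19 safety-relevant items. By the survey that prompted the call:

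- T1: no T2 or T3 data follow.
- T2: the T2 K10 and YSIS-3 are kept, with a T2 harm answer if section 2.11 is what is done; T3 is lost.
- T3: nothing is lost, because T3 has been completed.

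**Step 3: size for H9.** The Bud arm has 151 participants. At the planned 20% attrition, 151 × 0.8 = 120.8, about 121, reach T3. At the 60% retention threshold in Table 3, 151 × 0.6 = 90.6, about 91. The number rated imminent is not in the document; 1 to 3 is an assumption. Intervals are 95% Clopper-Pearson.

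| Summary | Estimate | 95% CI |
|---|---|---|
| No T3 harm reports, 20% attrition | 0/121 | 0 to 3.0% |
| No T3 harm reports, 60% retained | 0/91 | 0 to 4.0% |
| 1 imminent-risk case, all randomised | 1/151 = 0.7% | 0.0 to 3.6% |
| 2 cases | 2/151 = 1.3% | 0.2 to 4.7% |
| 3 cases | 3/151 = 2.0% | 0.4 to 5.7% |

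A second illustration sets aside ordinary attrition. Let w people be withdrawn, with harm-item rate p in those who stay and h in those withdrawn. The all-randomised rate is ((151 − w)p + wh)/151. With w = 2, p = 1% and h = 50% this is (1.49 + 1)/151 = 1.65%, against 1% reported. Over w = 1 to 4 and h = 25% to 100%, the rate runs from 1.2% to 3.6% when 1% is reported, and from 3.2% to 5.6% when 3% is reported. Here w, p and h are all assumed.

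**Step 4: size for the primary outcome.** Suppose 3 withdrawn participants, added to the 121 (124 in all), had T3 K10 scores 5 to 10 points above the model's prediction (assumption). The arm mean shifts by 3 × 5/124 = 0.12 to 3 × 10/124 = 0.24 points.

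**The case against.** The strongest reply is that this is a small table inconsistency joined to a clinical choice. Table 2 lists study measures and gives no row to the check-in offer at any time point, so it may simply not itemise the safety workflow. Its open feedback item, filed under acceptability and iatrogenic effects, is asked at T2, and K10 and YSIS-3 at T2 would catch many of those made to feel suicidal. That stands as far as it goes: the document does not show that the question will go unasked. The safety section and the printed schedule still disagree about it.

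On withdrawal, several stronger readings are tempting but unsupported:

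- *Those removed had deteriorated.* The K10 and ideation triggers are absolute levels, and the withdrawal decision is an absolute risk rating on a call. Someone at high risk since T1 and unchanged is also withdrawn.
- *The plan states that safety data stop.* It does not. This is the natural reading of being withdrawn from the study, with no sentence retaining follow-up.
- *H9 rests on the T3 items alone.* Section 2.9 names changes in ideation and adverse-event monitoring, and nothing says that an emergency withdrawal is left out of the safety report.
- *Intention-to-treat is breached.* Section 2.10.3 applies it to the analyses, with maximum likelihood on all available data. Withdrawn participants keep their arm and their observed scores.

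The rule also reaches only those who accept a voluntary call and are rated imminent, and ordinary attrition (about 30 of 151) removes far more people. Ending contact after an emergency is clinically defensible, and detailed adverse-event counting may sit in a fuller document. What remains is that three places fix withdrawal from the study and none separates stopping the intervention from stopping follow-up.

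**Conclusion.** The schedule conflict holds on the printed figures and needs no assumption: section 2.11 asks a harm question at T2, and the 54 items in Table 2 do not include it. Which of the two is right cannot be told from the article.

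The withdrawal point holds on the natural reading of the rule. The T3 harm summary will omit people selected on high suicide risk if they are withdrawn after a call prompted by T1 or T2. The effect is probably small in number, and T2 scores (for those withdrawn after T2) and adverse-event monitoring limit it. It matters for H9, where a few people can separate a report of none from a report of some. It does not threaten the primary K10 comparison: a shift of 0.12 to 0.24 points under the assumed inputs. Both are worth correcting; neither undermines the design.

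**What to change.** - **Table 2:** add the section 2.11 harm question at T2, with a T2 total of at least 55. If it is not in fact asked at T2, correct section 2.11 and its trigger instead.
- **Sections 2.4.2 and 2.11, Table 4:** replace withdrawal from the study with stopping the allocated intervention. Offer T3, or a short safety form (K10, YSIS-3 and the custom items), with consent and when clinically suitable.
- **H9 reporting:** report all post-randomisation imminent-risk cases by arm, over all randomised, as safety events, whether or not T3 is completed.

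The risk threshold, emergency response and referral stay the same.

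The cost is wording in four places, at least one extra T2 item, a form of at most 19 existing items, and an ethics amendment. Some participants will decline further contact after an emergency response; the count by arm still includes them, because it needs nothing more from them.
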